## **3.2 Exclusion Criteria**

- 3.2.1 Contraindication to receive IFN- $\gamma$  including known hypersensitivity to interferon-gamma, E. coli derived products or any component of the product
- 3.2.2 Subjects with a positive pregnancy test or who are breastfeeding
- 3.2.3 For men or women of childbearing potential (age < 50 without hysterectomy or oophorectomy or documented menopause), unwilling to use effective contraception for the duration of the study.
- 3.2.4 Primary engraftment failure
- 3.2.5 Active cardiac arrhythmias not controlled by medical management or current NYHA class II or higher congestive heart failure
- 3.2.6 Active ischemic heart disease not well controlled with medications
- 3.2.7 A seizure disorder not well controlled by medications
- 3.2.8 Estimated GFR <30 mL/min

3.2.9 AST/SGOT or ALT/SPOT > 5 x ULN

3.2.10 Total bilirubin > 3 x ULN

3.2.11 Chemotherapy (other than hypomethylating and/or venetoclax therapy, or targeted therapy such as IDH1/2 inhibitor or tyrosine kinase inhibitor) within the prior 4 weeks

3.2.12 Body surface area at or less than 1.5 m^2, or greater than 2.5 m^2 so as to minimize the variation in IFN-γ exposure based on differences in BSA.

### **3.3 Exclusion of children**

Patients less than 18 years of age will not be eligible in this study because of the potentially serious risks and limited information of the study intervention in children under the unique clinical setting after alloSCT. Also, the study investigators are not treating the minor subjects in our respective institution. Should the results of this trial demonstrate efficacy, consideration will be given to expanding accrual to this patient population.

### **3.4 Exclusion of pregnant or breast-feeding women**

There are no adequate studies of IFN-γ (Actimmune) in pregnant or breastfeeding women. It is not known whether IFN-γ (Actimmune) is excreted in human milk. Because we cannot exclude the potential for serious adverse reactions in fetuses or nursing infants, pregnant or breast-feeding women will be excluded from study participation.

## **4. RECRUITMENT AND REGISTRATION PROCEDURE**

### **4.1 Recruitment**

Patients will be primarily recruited through the clinical practitioners of the primary care team or members of the research team who will identify the patients who may be eligible for this protocol. Patients may also be recruited through ClinicalTrials.gov.

### **4.2 Registration**

Patients who meet the eligibility criteria will be consented by the research team. Demographic and clinical data will be collected in the Clinical Trials Management Application (CTMA) system.

External subjects will be registered centrally by the Coordinating Center. External sites must keep a log of subjects who have signed an informed consent document. Each external site must notify the Coordinating Center of subject consent within one business day of the consent. The Coordinating Center will enter the subject and consent date in the internal Clinical Trials Management Application (CTMA) for subject tracking.

External sites must verify subject eligibility prior to submitting screening documents to the Coordinating Center. All eligibility documents must be uploaded to a secure web-based

SharePoint for verification by the Coordinating Center. Relevant screening documents include:

Protocol Registration Form

Copy of the subject signed informed consent form

Eligibility Checklist signed by a First Reviewer and Investigator

All source documents needed to verify eligibility

All results collected per the Schedule of Assessments in Section 7 of the protocol

Source documents supporting stratification factors

As submission of pathology materials for diagnostic review and classification is mandatory, confirmation of tissue availability will be required prior to registration

Coordinating Center supplied source documents, as applicable

All requests for subject registration must be made at least 48 hours prior to the planned start of treatment date. The Coordinating Center will review all submitted documents for accuracy and verify all eligibility criteria are confirmed. The Coordinating Center will notify the external site by email of any discrepancies or requests for additional information, as applicable. A subject will not be registered until all outstanding discrepancies are adequately addressed and eligibility has been confirmed.

Once eligibility is confirmed, the Coordinating Center will register the subject in CTMA. The Coordinating Center will email the subject registration confirmation, including assigned subject ID, to the external site the day of subject registration.

Only eligible subjects will be enrolled. Exceptions to inclusion and exclusion criteria are not permitted. External sites should contact the UPMC HCC Sponsor and Coordinating Center for any questions regarding subject eligibility.

External sites must notify the Coordinating Center of screen failures or withdrawal of consent within one business day of the status change.

## **5. STUDY AGENTS INFORMATION**

### **5.1 Description**

5.1.1 Name: ACTIMMUNE (Interferon gamma-1b), supplied by Horizon Pharma USA

5.1.2 Manufacturing: ACTIMMUNE (Interferon gamma-1b) is a single-chain polypeptide containing 140 amino acids. Production of ACTIMMUNE is achieved by fermentation of a genetically engineered Escherichia coli bacterium containing the DNA which encodes for the recombinant protein. Purification of the product is achieved by conventional column chromatography. ACTIMMUNE is a highly purified sterile solution consisting of non-covalent dimers of two identical 16,465 Dalton monomers, with a specific activity of 20 million International Units/mg (2 x 10^6 International Units/0.5 mL) which is equivalent to 30 million units/mg.

## **5.2 Formulation and dose**

- 5.2.1 Dosage form: 100 mcg (2 million International Units) per 0.5 mL solution in a single-dose vial. ACTIMMUNE (interferon gamma-1b) is a sterile, clear, colorless solution filled in a single-dose vial for subcutaneous injection.
- 5.2.2 Route of administration: Subcutaneous injection
- 5.2.3 Dose regimen: 100 mcg three times weekly or per protocol guidance based on tolerability, response, or DLI infusions

## **5.3 Pharmacokinetics**

The intravenous, intramuscular, and subcutaneous pharmacokinetics of ACTIMMUNE has been investigated in 24 healthy male subjects following single-dose administration of 100 mcg/m^2 (twice the recommended dose for chronic granulomatous disease patients). ACTIMMUNE is rapidly cleared after intravenous administration (1.4 Liters/minute) and slowly absorbed after intramuscular or subcutaneous injection. After intramuscular or subcutaneous injection, the apparent fraction of dose absorbed was higher than 89%. The mean elimination half-life after intravenous administration of 100 mcg/m^2 in healthy male subjects was 38 minutes. The mean elimination half-lives for intramuscular and subcutaneous dosing with 100 mcg/m^2 were 2.9 and 5.9 hours, respectively. Peak plasma concentrations, determined by ELISA, occurred approximately 4 hours (1.5 ng/mL) after intramuscular dosing and 7 hours (0.6 ng/mL) after subcutaneous dosing. Multiple-dose subcutaneous pharmacokinetic studies were conducted in 38 healthy male subjects. There was no accumulation of ACTIMMUNE after 12 consecutive daily injections of 100 mcg/m^2. Interferon-gamma was not detected in the urine of healthy human volunteers following administration of 100 mcg/m^2 of ACTIMMUNE by the intravenous, intramuscular, and subcutaneous routes. In vitro perfusion studies utilizing rabbit livers and kidneys demonstrate that these organs are capable of clearing interferon-gamma from perfusate.

## **5.4 Toxicity**

- 5.4.1 Carcinogenesis: ACTIMMUNE has not been tested for its carcinogenic potential.
- 5.4.2 Mutagenesis: Ames tests using five different tester strains of bacteria with and without metabolic activation revealed no evidence of mutagenic potential. ACTIMMUNE was tested in a micronucleus assay for its ability to induce chromosomal damage in bone marrow cells of mice following two intravenous doses of 20 mg/kg. No evidence of chromosomal damage was noted.

- 5.4.3 Fertility: Female cynomolgus monkeys treated with daily subcutaneous doses of 30 or 150 mcg/kg ACTIMMUNE (approximately 20 and 100 times the human dose) exhibited irregular menstrual cycles or absence of cyclicity during treatment. Similar findings were not observed in animals treated with 3 mcg/kg ACTIMMUNE. Female mice receiving recombinant murine IFN-interferon gamma (rmuIFN-gamma) at 32 times the maximum recommended clinical dose of ACTIMMUNE for 4 weeks via intramuscular injection exhibited an increased incidence of atretic ovarian follicles. Male cynomolgus monkeys treated intravenously for 4 weeks, with 8 times the maximum recommended clinical dose of ACTIMMUNE showed decreased spermatogenesis. Male mice receiving rmuIFN-gamma at 32 times the maximum recommended clinical dose of ACTIMMUNE for 4 weeks via intramuscular injection exhibited reduced spermatogenesis. The impact of this finding on fertility is not known. Male mice treated subcutaneously with rmuIFN-gamma from shortly after birth through puberty, with 280 times the maximum recommended clinical dose of ACTIMMUNE exhibited profound yet reversible decreases in sperm counts and fertility and an increase in the number of abnormal sperm. The clinical significance of these findings observed following treatment of mice with rmuIFN-gamma is uncertain.

## 5.5 Clinical adverse events

- 5.5.1 Cardiovascular Disorders: Acute and transient “flu-like” symptoms such as fever and chills induced by ACTIMMUNE at doses of 250 mcg/m^2/day (greater than 10 times the weekly recommended dose) or higher may exacerbate pre-existing cardiac conditions. Patients with pre-existing cardiac conditions, including ischemia, congestive heart failure, or arrhythmia on ACTIMMUNE, should be monitored for signs/symptoms of exacerbation. Some of “flu-like” symptoms may be minimized by bedtime administration of ACTIMMUNE. Acetaminophen may also be used to ameliorate these effects.
- 5.5.2 Neurologic Disorders: Decreased mental status, gait disturbance, and dizziness have been observed, particularly in patients receiving ACTIMMUNE doses greater than 250 mcg/m^2/day (greater than 10 times the weekly recommended dose). Most of these abnormalities were reversible within a few days upon dose reduction or discontinuation of therapy. Monitoring of patients with seizure disorders or other central nervous system disorders is recommended when administering ACTIMMUNE.
- 5.5.3 Bone Marrow Toxicity: Reversible neutropenia and thrombocytopenia that can be severe and may be dose-related have been observed during ACTIMMUNE therapy.

- 5.5.4 Hepatic Toxicity: Repeated administration of ACTIMMUNE to patients with advanced hepatic disease may result in the accumulation of interferon-gamma-1b. Frequent assessment of liver function in these patients is recommended. Elevations of aspartate transaminase (AST) and/or alanine transaminase (ALT) (up to 25-fold) have been observed during ACTIMMUNE therapy.
- 5.5.5 Hypersensitivity Reactions: Isolated cases of acute serious hypersensitivity reactions have been observed in patients receiving ACTIMMUNE. If such an acute reaction develops, the drug should be discontinued immediately and appropriate medical therapy instituted. Transient cutaneous rashes have occurred in some patients following the injection of ACTIMMUNE that have necessitated treatment interruption.
- 5.5.6 Renal Toxicity: Monitor renal function regularly when administering ACTIMMUNE in patients with severe renal insufficiency because the possibility exists that with repeated administration, accumulation of interferon gamma-1b may occur. Renal toxicity has been reported in patients receiving ACTIMMUNE.
- 5.5.7 Allergic Reactions to Natural Rubber: The stopper of the glass vial for ACTIMMUNE contains natural rubber (a derivative of latex), which may cause allergic reactions.

## **5.6 Storage**

The vials should be stored in the refrigerator at 2 to 8 °C (36 °F to 46 °F). Do Not Freeze. Avoid excessive or vigorous agitation. Do Not Shake. An unused vial of ACTIMMUNE can be stored at room temperature up to 12 hours prior to use. Discard vials if not used within the 12-hour period. Do not return to the refrigerator

## **6. TREATMENT PLAN AND STUDY PROCEDURES**

### **6.1 Clinical Data Collection**

Each subject will be assigned a research code number. Data that are part of the eligibility checklist and contact information will be stored in the password-protected Clinical Trials Management Application (CTMA) database system at each site. The information linking the research code numbers to the patients' identities will be accessible only to the registry investigators and staff. No Protected Health Information or personal identifiers will be transferred between the University of Pittsburgh and Fred Hutchinson Cancer Research Center.

### **6.2 Pre-Treatment Clinical Evaluation (within 2 weeks of treatment unless specified)**

After a subject signs informed consent, the procedures listed below will be performed within two weeks prior to treatment. The schedule of events is summarized in **Section 15, Appendix C**

#### **6.2.1 History, physical exam, and performance status**

- History of primary disease and treatment
- Past medical history
- Performance status (ECOG and Karnofsky scale)

- Physical examination
- Concurrent medication
- Pre-existing symptoms and signs using CTCAE version 5.0 or equivalent

#### 6.2.2 Assessment of history and active GVHD

- Past and current acute GVHD using CIBMTR grading system (Appendix A)
- Past and current chronic GVHD using NIH scoring system (Appendix B)
- GVHD prophylaxis
- Treatment of GVHD

#### 6.2.3 Information on allogeneic stem cell transplantation

- Transplant related clinical information HLA typing (donor and recipient)
- Pre-transplant co-morbidity and HCT-comorbidity index (recipient, if available)
- Demographics: age, gender, race (donor and recipient)
- Type of stem cells, the dose of total nuclear cells, CD34 cells, and T cells in the graft (if available)
- Pre-transplant infection serology profiling (donor and recipient): CMV, EBV, Toxoplasma, and hepatitis
- Blood type and antibody screen (donor and recipient)
- HLA-alloantibody (donor and recipient, only if available)
- Conditioning regimen before the transplant
- Post-transplant treatment including chemotherapy, targeted kinase inhibitors, cell therapy
- History of infections
- History of transplant-related complications
- History of graft failure

#### 6.2.4 Bone marrow aspirate and biopsy – This can be the same bone marrow sample as was used to assess eligibility or in the course of routine clinical care if done within two weeks of treatment initiation. A single sample collection consent form can be used prior to official enrollment for the study in order to obtain a research sample from this bone marrow aspirate in patients being considered for participation in this study within two weeks.

- Morphologic and flow cytometric assessment of the malignant blast percentage and evidence of dysplasia in subjects with MDS
- Chromosome analysis, if clinically indicated
- Minimal residual disease markers by any methodology
- BCR-ABL (CML, and Ph+ AML only), PML-RAR $\alpha$  (APL only)
- Myeloid panel (AML or MDS-specific) next-generation sequencing if clinically available under the standard care.

#### 6.2.5 Laboratory testing

- Pregnancy test (serum or urine) for women of child-bearing age

- CBC with differential, chemistry panel (Na, K, Cl, CO2, creatinine, glucose, urea nitrogen, phosphorus, magnesium, albumin, calcium, LDH, uric acid), hepatic (alkaline phosphatase, ALT, AST, and total bilirubin)
- STR chimerism of peripheral blood (CD3+ and CD33+ myeloid)

### **6.3 Stage 1: Safety evaluation of a fixed dose of IFN- $\gamma$**

#### **6.3.1 Clinical assessment before the first dose of IFN- $\gamma$**

- Before the first dose of IFN- $\gamma$ , the study team or patient's treating clinical team will take vital signs (temperature, blood pressure, and heart rate) and history of symptoms related to exclusion criteria for the first administration of IFN- $\gamma$ , as listed below.
- The symptoms/signs which will disqualify the subjects from receiving the first dose of IFN- $\gamma$  include
  - Flu-like symptoms within the past 48 hours
  - Fever  $\geq 38.0$  within the past 48 hours
  - Hypotension systolic BP  $< 90$  mmHg
  - Diarrhea or vomiting within the past 48 hours if outside the patient's established pattern of GI recovery or GI side effects post-transplant
  - Other symptoms suggesting active acute infections within the past 48 hours
  - Finding consistent with GVHD that exceeds inclusion criteria
- Subjects deemed ineligible for the first IFN- $\gamma$  due to infectious symptoms can be reassessed at a later time.

#### **6.3.2 Dose adjustments of IFN- $\gamma$**

- The initial dose of IFN- $\gamma$  will be a 100 mcg fixed-dose three times per week.
- Each dose will be administered subcutaneously using a needle size as per institutional standard. Subsequent doses of IFN- $\gamma$  will be administered to different locations in either arm, abdomen, or thigh.
- The first dose of IFN- $\gamma$  will be administered by one of the clinical staff, nurses, or research staff at Hillman Cancer Center. At Seattle Cancer Care Alliance or the University of Washington Medical Center, IFN- $\gamma$  will be administered by clinical nursing staff. At the first visit to the clinic, the patient will receive the self-injection training for the subsequent administration of IFN- $\gamma$  at home. The self-injection training can be repeated at a subsequent visit if necessary. The IFN- $\gamma$  injection diary will be recorded by the subject.
- Acetaminophen 650mg with or without prochlorperazine 5-10mg as pre-medication can be given before each dose of Actimmune at physician's discretion
- Schedule of IFN- $\gamma$  and dose adjustment for cohort 1 (Figure 4)

##### **1) The initial dose of IFN- $\gamma$**

- a. The first dose of IFN- $\gamma$  100 mcg will be administered on day 0 in the clinic.
  - b. The subject will continue self-injection of 100mcg, three times a week for two weeks (e.g., Monday, Wednesday, Friday or Tuesday, Thursday, Saturday)
- 2) 48 hours after the initial dose of IFN- $\gamma$  (up to 1 week)
- a. Bone marrow aspirate (no biopsy) will be performed for morphology, flow cytometry, and a research sample. (Cytogenetics/molecular testing only needed if clinically indicated to follow MRD.)
- 3) Two weeks after the initial dose of IFN- $\gamma$  (window: +/- 5 days)
- a. If 100 mcg per day three times a week is tolerated, the subject will continue IFN- $\gamma$  for the next two weeks.
  - b. If the subject is not tolerating at the dose of 100mcg per day three times a week for the first two weeks, decrease to 100 mcg two times a week for two weeks.
- 4) Four weeks after the initial dose of IFN- $\gamma$
- a. Subjects tolerating 100 mcg three times a week can proceed to DLI if eligible.
  - b. If the subject is not tolerating a given dose, it can be decreased to 100mcg two times a week for another two weeks (+/- 5 days). If tolerated, the patient would then be eligible to proceed to the DLI phase.
  - c. If 100 mcg two times per week is not tolerated, IFN- $\gamma$  will be discontinued, and the subject will be withdrawn from further on-study treatment. The subject may still proceed to DLI off study.

[figure not shown]

**Figure 4. The dose adjustment plan for IFN- $\gamma$  for cohort 1.**

- Schedule of IFN- $\gamma$  and dose adjustment for cohort 2 (Figure 5)
- 1) The initial dose of IFN- $\gamma$
- a. The first dose of IFN- $\gamma$  100 mcg will be administered on day 0 in the clinic.
  - b. The subject will continue self-injection of 100mcg, three times a week for two weeks (e.g., Monday, Wednesday, Friday or Tuesday, Thursday, Saturday)

- 2) 48 hours after the initial dose of IFN- $\gamma$  (up to 1 week)
  - a. Bone marrow aspirate (no biopsy) will be performed for morphology, flow cytometry, and a research sample. (Cytogenetics/molecular testing only needed if clinically indicated to follow MRD.)
- 3) One week after the initial dose of IFN- $\gamma$  (window: - 3 days to + 7 days)
  - a. Subjects tolerating 100 mcg three times a week can proceed to DLI if eligible.
  - b. If the subject is not tolerating a given dose, it can be decreased to 100mcg two times a week for one week (+/- 5 days). If tolerated, the patient would then be eligible to proceed to the DLI phase.
  - c. If 100 mcg two times per week is not tolerated, IFN- $\gamma$  will be discontinued, and the subject will be withdrawn from further on-study treatment. The subject may still proceed to DLI off study.

[figure not shown]

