#### 6.5.1.3 Protocol visit #2: Stage 1, minimally 48 hours (up to one week) after the first dose of IFN- $\gamma$ : Safety and biological assessment of IFN- $\gamma$ , bone marrow aspiration for research

- Clinical safety monitoring: Any reaction or symptoms related to the prior doses of IFN- $\gamma$  and will be assessed specifically focusing on active grade II-IV GVHD or de novo grade III-IV, or progressive chronic GVHD
- **Bone marrow aspirates** (no biopsy) will be performed for morphology, flow cytometry, and research sample (10mL).
- Research sample collection: 10mL of bone marrow (10ml green top heparin tube), 30 mL of peripheral blood (10 mL green top heparin tube x 3 tubes) will be collected.
- The subsequent doses of IFN- $\gamma$  will be administered after the safety assessment.

6.5.1.4 Protocol visit #3: Stage 1, Day +14 ( $\pm$  5 days) after the first dose of IFN- $\gamma$ : Safety assessment of IFN- $\gamma$

- Clinical safety monitoring: Any reaction or symptoms related to the prior doses of IFN- $\gamma$  and will be assessed specifically focusing on active grade II-IV GVHD or de novo grade III-IV, or progressive chronic GVHD
- Laboratory monitoring: CBC with differential, chemistry panel (Na, K, Cl, CO2, creatinine, glucose, urea nitrogen, phosphorus, magnesium, albumin, calcium, LDH, uric acid), hepatic (alkaline phosphatase, ALT, AST, and total bilirubin ) panel
- The subsequent doses of IFN- $\gamma$  will be administered after safety assessment.

6.5.1.5 Protocol visit #4: End of stage 1 and pre-treatment evaluation for stage 2 (donor lymphocyte infusion), day +28 ( $\pm$  5 days) after the first dose of IFN- $\gamma$  or two weeks ( $\pm$  5 days) after a stable dose of IFN- $\gamma$ :

- Clinical safety monitoring: Any reaction or symptoms related to the prior doses of IFN- $\gamma$  and will be assessed specifically focusing on active grade II-IV GVHD or de novo grade III-IV, or progressive chronic GVHD
- Laboratory monitoring: CBC with differential, chemistry panel (Na, K, Cl, CO2, creatinine, glucose, urea nitrogen, phosphorus, magnesium, albumin, calcium, LDH, uric acid), hepatic (alkaline phosphatase, ALT, AST, and total bilirubin) panel
- STR chimerism of bone marrow (if collected) and peripheral blood (whole blood, or CD3 and myeloid)

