#### 6.5.2.2 Protocol visit #1: Stage 1, the first dose of IFN- $\gamma$

- Pre-treatment assessment (bone marrow aspirates, vital signs, and clinical assessment) as described in 6.3.1 will be performed before IFN- $\gamma$  administration.
- **Bone marrow aspirates** (no biopsy) will be performed for morphology, flow cytometry, and research sample (10mL) if the bone marrow research sample is not collected within two weeks before the first dose of IFN- $\gamma$ .
- Research sample collection: A bone marrow aspirate with a goal of 10 mL collected (in 10ml green top heparin tube x 1) and 30 mL of peripheral blood (10 mL green top heparin tube x 3 tubes) will be obtained as a baseline sample before IFN- $\gamma$  administration.
- First dose of IFN- $\gamma$  will be administered after the safety assessment.
- As described in 6.3.1., the patient will receive the training for self-injection of IFN- $\gamma$
- Safety monitoring: Subjects will be assessed for an acute reaction to the IFN- $\gamma$  or complication of biospecimen collection. Subjects will stay in the clinic for at least 1 hour after IFN- $\gamma$  administration and be assessed by a physician, physician assistant, advanced practice nurse or nurse prior to discharge from the clinic.

6.5.2.3 Protocol visit #2: Stage 1, minimally 48 hours (up to one week) after the first dose of IFN- $\gamma$ : Safety and biological assessment of IFN- $\gamma$ , bone marrow aspiration for research

- Clinical safety monitoring: Any reaction or symptoms related to the prior doses of IFN- $\gamma$  and will be assessed specifically focusing on active grade II-IV GVHD or de novo grade III-IV, or progressive chronic GVHD
- **Bone marrow aspirates** (no biopsy) will be performed for morphology, flow cytometry, and research sample (10mL).
- Research sample collection: 10mL of bone marrow (10ml green top heparin tube), 30 mL of peripheral blood (10 mL green top heparin tube x 3 tubes) will be collected.
- The subsequent doses of IFN- $\gamma$  will be administered after the safety assessment.

6.5.2.4 Protocol visit #3: End of stage 1 and pre-treatment evaluation for stage 2 (donor lymphocyte infusion), Day +7 (-3 days to +5 days) after the first dose of IFN- $\gamma$ : Safety assessment of IFN- $\gamma$

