- Clinical safety monitoring: Any reaction or symptoms related to the prior doses of IFN- $\gamma$  and will be assessed specifically focusing on active grade II-IV GVHD or de novo grade III-IV, or progressive chronic GVHD
- Laboratory monitoring: CBC with differential, chemistry panel (Na, K, Cl, CO2, creatinine, glucose, urea nitrogen, phosphorus, magnesium, albumin, calcium, LDH, uric acid), hepatic (alkaline phosphatase, ALT, AST, and total bilirubin) panel
- The subsequent doses of IFN- $\gamma$  will be administered after the safety assessment.
- If DLI is available, the first dose of DLI will be infused within two weeks from this visit.

6.5.2.5 Protocol visit #4: Stage 2 first safety assessment, 21 days (+/- 5 days) after the first dose of IFN- $\gamma$ , or 14 days (+/- 5 days) after the first dose of DLI.

- Clinical safety monitoring: Any reaction or symptoms related to the IFN- $\gamma$  or DLI will be assessed, specifically focusing on active grade II-IV GVHD or de novo grade III-IV, or progressive chronic GVHD
- Laboratory monitoring: CBC with differential, chemistry panel (Na, K, Cl, CO2, creatinine, glucose, urea nitrogen, phosphorus, magnesium, albumin, calcium, LDH, uric acid), hepatic (alkaline phosphatase, ALT, AST, and total bilirubin) panel
- The subsequent frequency IFN- $\gamma$  will be reduced to once-weekly dosing for four more weeks.

6.5.2.6 Protocol visit #5: Stage 2 follow up safety assessment, 35 days (+/- 5 days) after the first dose of IFN- $\gamma$ , or 28 days (+/- 5 days) after the first dose of DLI

- Clinical safety monitoring: Any reaction or symptoms related to the IFN- $\gamma$  or DLI will be assessed, specifically focusing on active grade II-IV GVHD or de novo grade III-IV, or progressive chronic GVHD
- Laboratory monitoring: CBC with differential, chemistry panel (Na, K, Cl, CO2, creatinine, glucose, urea nitrogen, phosphorus, magnesium, albumin, calcium, LDH, uric acid), hepatic (alkaline phosphatase, ALT, AST, and total bilirubin) panel
- STR chimerism of bone marrow (if collected) and peripheral blood (whole blood, or CD3 and myeloid)
- Research sample collection: 30 mL of peripheral blood (10 mL green top heparin tube x

3 tubes) will be collected.

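### Cohort 2's one-week reduced-frequency period before DLI may run from 2 to 12 days, and the pre-DLI visit is not re-dated after a step-down

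*Protocol*

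**What the plan says.** **Step-down, cohort 2 (Protocol 6.3.2, step 3b).** A patient not tolerating the given dose goes to twice-weekly injections: "it can be decreased to 100mcg two times a week for one week (+/- 5 days"). The consequence is "If tolerated, the patient would then be eligible to proceed to the DLI phase". No number of injections is attached. Section 6.3.2 times this decision at one week with "window: - 3 days to + 7 days".

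**Step-down, cohort 1 (6.3.2, step 4b).** The frequency can be "decreased to 100mcg two times a week for another two weeks (+/- 5 days"). The tolerance is the same, on a period twice as long.

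**Pre-DLI visit.** In cohort 2, visit #3 (6.5.2.4) closes stage 1 and is the evaluation before DLI. Its only date is "Day +7 (-3 days to +5 days"), and Appendix D repeats that window. The same section adds: "If DLI is available, the first dose of DLI will be infused within two weeks from this visit". In cohort 1, visit #4 (6.5.1.5) is set at day +28 but may instead be held two weeks (± 5 days) "after a stable dose of" IFN-γ. Both visits include blood count, chemistry and hepatic panels.

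**Next cohort 2 visit.** Visit #4 (6.5.2.5) is the first stage 2 safety assessment, at day 21 ± 5 or 14 ± 5 days after the first DLI.

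**Other conditions.** The DLI condition in 6.4.1.3 concerns graft-versus-host disease (GVHD). Intolerance in 6.6.1 also includes new AST or ALT elevation of grade 3 or more and estimated GFR below 30 mL/min (6.6.1.2).

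**The concern.** The primary safety objective (1.1.2) confines the combination to patients who have tolerated IFN-γ alone. Cohort 2 shortens the monotherapy lead-in to one week, so more rests on how tolerance is established. For patients just judged intolerant, the protocol allows a very short period at the reduced frequency and does not re-date the visit at which tolerance would be judged.

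A patient stepped down at visit #3 for a liver or renal value has no scheduled repeat panel designated as the check before DLI. Such a patient would enter the combination safety summary as having tolerated monotherapy, with no defined exposure or assessment behind that label.

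**Working it through.** No sample-size or error-rate formula applies. The check is arithmetic on the windows.

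**1. Length of the reduced-frequency period.**
- Cohort 2: 7 − 5 = 2 days to 7 + 5 = 12 days. The tolerance is 5/7 = 71% of the nominal period.
- Cohort 1: 14 − 5 = 9 days to 14 + 5 = 19 days. The tolerance is 5/14 = 36%.

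**2. Injections in the period.** The average at twice weekly is days × 2/7. The range assumes alternating 3- and 4-day gaps, which the protocol does not state, and covers every possible start day.

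| Period | Average | Range at 3/4-day gaps |
|---|---|---|
| Cohort 2 shortest, 2 days | 2 × 2/7 = 0.57 | 0 to 1 |
| Cohort 2 longest, 12 days | 12 × 2/7 = 3.43 | 3 to 4 |
| Cohort 1 shortest, 9 days | 9 × 2/7 = 2.57 | 2 to 3 |
| Cohort 1 longest, 19 days | 19 × 2/7 = 5.43 | 5 to 6 |

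Two injections fit into the 2-day minimum only if given on consecutive days, or 48 hours apart with both end days counted. The nominal week holds two.

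**3. Decision date.** Section 6.3.2 gives day 7 − 3 = 4 to 7 + 7 = 14. Section 6.5.2.4 and Appendix D give day 4 to 7 + 5 = 12. These disagree.

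**4. End of the period against the next visit.** Visit #4 opens on day 21 − 5 = 16 under its day-21 anchor. Taking the step-down from visit #3 (days 4 to 12, nine possible dates):
- 2-day period: ends on days 6 to 14, before day 16 for all nine dates.
- 7-day period: ends on days 11 to 19, before day 16 when visit #3 is on days 4 to 8, which is five of nine dates. From day 7 it ends on day 14.
- 12-day period: ends on days 16 to 24, so never before visit #4 can open.

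With the wider 6.3.2 window (days 4 to 14, eleven dates), the 7-day period ends before day 16 for five of eleven.

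**5. Visits between step-down and DLI.** DLI is due within 14 days of visit #3. No visit is designated for the end of the reduced-frequency period. Visit #2 (day 2 to 7) could serve only if held out of sequence after an early visit #3, and 6.5.2.3 lists no chemistry or hepatic panel for it.

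**The case against.** Two days is the permitted edge, not the plan. The plan is one week, nominally two injections, and ± 5 days may be ordinary scheduling slack. That stands, but a window of 71% of the period does not protect the plan.

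Four stronger readings are tempting, and the documents do not support them:
- **That a patient can pass after at most one injection.** This needs a spacing rule, and the protocol gives none for twice-weekly dosing.
- **That no visit or panel can ever fall before DLI.** Visit #4 may be dated from the first IFN-γ dose. If visit #3 is on days 9 to 12, a one-week period ends on days 16 to 19, inside visit #4's window and possibly before a late DLI. Visit #4 is still not designated as the pre-DLI evaluation.
- **That the gate is simply passed untested.** GVHD-type intolerance is largely caught again by 6.4.1.3, and 6.7 allows discontinuation at the physician's discretion. Section 6.7 also covers grade 3 or 4 organ dysfunction unresolved after two weeks, but that allowance can still be running when DLI is due. What remains open is symptomatic and laboratory-defined intolerance.
- **That the window was copied from cohort 1 by mistake.** The protocol does not give its drafting history.

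The cohort 1 comparison also has limits. The alternative date in 6.5.1.5 is permissive, and Appendix C lists visit #4 only at day 28 ± 5. Nor would a longer period make post-DLI events attributable: 6.9.1 accepts that cytopenia, GVHD and infection may come from IFN-γ, DLI or the transplant.

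**Conclusion.** The point holds in a limited form. As written, 2 to 12 days at the reduced frequency can qualify a patient just judged intolerant for DLI, against 9 to 19 days in cohort 1. At the lower bound this may mean 0 or 1 injection, assuming roughly even spacing.

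Unlike cohort 1's visit, cohort 2's pre-DLI visit does not move with a dose change. At the nominal one-week length, for most visit #3 dates (five of nine, day 7 included), the period ends before the next visit can open. The GVHD condition on DLI does not cover the AST/ALT and GFR criteria for intolerance.

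The protocol gives no rate for step-downs, so the expected effect cannot be stated. If one stepped-down patient did receive DLI, that patient would be 1/6 = 17% to 1/3 = 33% of the cohort 2 combination summary, taking three to six DLI recipients from 8.2.1. In a descriptive pilot this affects what the label of tolerated monotherapy means; it does not affect an error rate.

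**What to change.** - Reconcile the ± 5-day window in step 3b with the one-week period it qualifies and with the timing of the pre-DLI visit. Also reconcile the decision window in 6.3.2 (−3/+7 days) with 6.5.2.4 and Appendix D (−3/+5 days).
- Add to 6.5.2.4 and Appendix D an alternative visit #3 date after a dose change, like the one in 6.5.1.5. The existing assessment and panels would then cover stepped-down patients before DLI.
- Using the injection diary already required in 6.3.2, report for each DLI recipient the injections received before DLI at the tolerated frequency.

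What counts clinically as tolerated is for the investigators; no minimum exposure is proposed here.

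The cost is amendment wording, one existing visit moved or repeated in stepped-down patients, and possibly a few days' delay to their DLI.
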